# Self-directed arm-crank exercise to improve volitional control of the trunk in patients with subacute spinal cord injury: a multicentre, parallel-group, randomised controlled trial protocol

**DOI:** 10.1136/bmjopen-2024-092226

**Published:** 2025-08-21

**Keywords:** Neurophysiology, Physical Therapy Modalities, Clinical Trial, Posture, Quality of Life

## Abstract

**ABSTRACT:**

**Introduction:**

A spinal cord injury (SCI) disrupts synaptic connections between the corticospinal tract and motor neurons, impairing muscle control below the injury site. Many individuals with an SCI have impaired trunk control, affecting the performance of activities of daily living and quality of life. Work has shown improvements in trunk control after home-based, unsupervised arm-crank exercise training (ACET) in people with chronic motor-incomplete SCI. However, no studies have examined ACET’s impact on trunk control in individuals with subacute SCI. This study aims to investigate ACET’s effects on trunk control in adults with subacute incomplete SCI, and its mechanisms, and its long-term benefits on neuropathic pain, psychological well-being, physical activity levels and health-related quality of life.

**Methods and analysis:**

This multicentre, parallel-group, randomised controlled trial will evaluate self-directed ACET in 60 individuals with subacute SCI (<6 months postinjury). All participants will receive standard in-patient rehabilitation; the intervention group will additionally undertake a progressive ACET protocol for 8 weeks. Assessments will occur at baseline (T0), 4 weeks (T1), postintervention (T2) and 6-month follow-up (T3). Outcomes include static and dynamic sitting balance with kinematic measurements and high-density electromyography of the erector spinae, corticospinal excitability, muscle strength, functional independence and questionnaires of neuropathic pain, psychological well-being, self-efficacy and motivation, physical activity and health-related quality of life. Quantitative data will be analysed using mixed-model repeated measures ANOVAs and Student’s t-tests. Thematic analysis will be conducted on qualitative data obtained from focus groups in which the feasibility, enablers and challenges of ACET for individuals with subacute SCI will be discussed.

**Ethics and dissemination:**

This study was approved by The Health Research Authority and Health and Care Research Wales (22/NS/0054). Results will be published in peer-reviewed journals. Findings will be presented at National and International conferences for researchers and clinicians. Finally, results will be disseminated to the SCI community.

**Trial registration number:**

ISRCTN17247972

STRENGTHS AND LIMITATIONS OF THIS STUDYThis multicentre, randomised controlled trial will evaluate trunk control over time in individuals with spinal cord injury (SCI) following a self-directed exercise programme, compared with those receiving standard care.The study assesses the broader impact of the intervention on individuals’ health and functioning, including impairments, activities, participation and environmental and personal factors.The study will use both quantitative and qualitative methods to enable multidimensional evaluation of patients’ responses to the intervention.A limitation is that neither the participants nor assessors are blinded to group allocation, which may introduce bias to the results.

## Introduction

 A spinal cord injury (SCI) damages synaptic connections between the corticospinal tract and motor neurons in the spinal cord, resulting in impaired volitional control of muscles and function below the site of injury.^1^ Globally, there are approximately 15.4 million people living with this devastating injury.^2^ In the United Kingdom alone, it is estimated that 104 000 people are living with SCI, with 4400 new cases reported every year.^3^

Trunk muscles are involved in a number of activities of daily living, such as reaching out for an object,^4^ moving the upper limbs^5^ and transfer.^6^ Most people with SCI have impaired trunk control which can compromise independence in daily activities, including stability, feeding and dressing.^7^,^10^ People in this condition may instead rely on their upper limbs to maintain stability or use compensatory postural control strategies,^4 11^ highlighting the importance of targeted trunk training to recover function and independence after SCI.

Research has suggested that upper-body exercise training improved trunk control in people with chronic SCI.^12^,^14^ For example, work showed improved dynamic sitting balance, accompanied by increased activity of the erector spinae (ES) and corticospinal excitability of the ES, after home-based, unsupervised ACET in individuals with chronic motor incomplete SCI.^12^ The underlying mechanisms could be related to use of shared neural circuits, such as crossed corticospinal facilitation, between the upper limbs and the trunk.^15 16^ This neural interaction has been shown to be preserved in people with incomplete SCI.^5^ Evidence has suggested that strengthening corticospinal connections in the spinal cord may lead to functional improvement in humans with chronic SCI.^17^,^19^

In the early stages following injury, research in animals with SCI showed sprouting of corticospinal axons rostral and caudal to the lesion site, forming alternative neural circuits to maintain supraspinal influence on motor neurons below the injury.^20^,^22^ Exercise interventions in rats with SCI increase the levels of neurotrophins that overcome myelin-derived axon growth inhibitors^23^ and promote synaptic plasticity in the spinal cord, creating new circuits to restore function.^24 25^ Similarly, evidence in humans with SCI has suggested the benefits of early motor training for promoting recovery of limb function.^26^,^28^ Given that neural pathways undergo extensive reorganisation during the early stages of SCI,^29^ particularly when the injury is incomplete,^30^ it is logical to hypothesise that the therapeutic effects of early ACET will be even greater in individuals with subacute SCI.

In addition to the physical benefits, exercise has been shown to improve pain and psychological symptoms in both general and clinical populations.^31 32^ People living with SCI experience higher levels of neuropathic pain,^33^ anxiety and depression compared with those without.^34^ However, low levels of exercise self-efficacy (ESE) in people with SCI^34^ on often decrease adherence and maintenance to exercise, thus hindering recovery.^35^

We are not aware of any studies investigating self-directed ACET and its effects on trunk control in individuals with subacute SCI. Hence, the primary aims of the study are to investigate the effects of ACET on volitional control of the trunk, and the neurophysiological mechanisms underpinning these effects in adults with subacute incomplete SCI. The secondary aims of the study are to evaluate short- and long-term benefits of the ACET on neuropathic pain, psychological well-being, and physical activity in this population. Additionally, self-efficacy and motivation of individuals with SCI for engaging in the ACET will be examined as potential predictors of adherence and the outcomes. This is important because people with SCI often experience higher levels of neuropathic pain,^33^ anxiety and depression compared with those without.^34^ However, low levels of ESE in people with SCI^34^ on often decrease adherence and maintenance to exercise, thus hindering recovery.^35^ Furthermore, we will investigate long-term translational effects of ACET on leisure time physical activity and health-related quality of life.

The objectives of the study are:

To assess static and dynamic sitting balance after 8 weeks of ACET in individuals with subacute incomplete SCI.To examine training-induced changes in activation of the ES during static and dynamic sitting balance tasks and excitability of the corticospinal axons projecting to the ES in individuals with subacute incomplete SCI.To evaluate neuropathic pain, psychological well-being, physical activity, independence, muscle strength and health related quality of life in individuals with a subacute incomplete SCI.To predict adherence to the ACET and outcomes using individuals’ self-efficacy and motivation.

## Methods and analysis

### Study design

This study is a multicentre, two parallel-group, non-blinded, randomised controlled trial of a self-directed ACET in individuals with subacute SCI (<6 months postinjury). The study was approved by the North of Scotland Research Ethics Committee (1) (22/NS/0054) and prospectively registered on the International Standard Randomised Controlled Trial Number registry (ISRCTN17247972). This research is the second part of a larger trial which consists of a feasibility study (ISRCTN89333770; completed) and a randomised control trial (this study). The study will be conducted in accordance with the Declaration of Helsinki. The study protocol is reported following the SPIRIT checklist (online supplemental appendix 1).

### Patient and public involvement

Patient and public involvement group: Participants who took part in the feasibility study were involved in the protocol design. The new cohort will be involved in results interpretation and development of the next trial.

### Recruitment and consent process

Recruitment will be conducted at the Princess Royal Spinal Cord Injuries Centre (PRSCIC) and at the Yorkshire Regional Spinal Injuries Centre (YRSIC). Recruitment will be carried out by the medical team of the spinal units. Patients who meet the eligibility criteria will be approached by a member of the medical team and given a copy of the participant information sheet to read. They will be given at least 24 hours to consider their participation to the study. Prior to the consent process, potential participants will be given the opportunity to ask the research team questions regarding the study. The research team will obtain written informed consent from all participants prior to any data collection.

### Study population and sample size

The sample size was based on the effect size drawn from the feasibility study reporting an improvement in angular displacement of the trunk during forward reaching with ACET compared with the standard of care, with a large effect size (Cohen’s d = 0.85). An a priori power calculation suggested that a sample size of 46 patients with SCI, 23 in each group, is sufficient to detect a between-group difference for the primary outcome measure, using an independent t-test with 80% power and a 5% level of significance. To account for a 6-month follow-up after discharge, a 30% conservative dropout rate was considered. Hence, 60 participants in total will be recruited for this study.

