### Randomisation

All participants will undergo one baseline assessment and one 4-week assessment to estimate individuals’ spontaneous recovery rate. After the 4-week assessment, participants will be randomly allocated (1:1) to an ACET group or a standard care control group using a minimisation randomisation^41^ to balance covariates of level of injury and classification of injury between groups. The procedure will start from the first participant being allocated to a study group at random. For each subsequent participant, we determine which study group would lead to better balance between the groups in the variables of interest. The randomisation will be performed by [name] who will not be involved in recruitment of participants. However, it is not achievable in this study to blind participants or researchers conducting the assessments given the type of the intervention and resources available. Figure 1 illustrates the trial flow chart.

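### Sixty recruits less the stated 30% dropout leave 42 evaluable participants, not the 46 that the protocol says it needs for 80% power

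*Protocol article*

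**What the plan says.** Under *Study population and sample size*, the protocol article takes an effect size of d = 0.85 from the feasibility study, for trunk angular displacement during forward reaching. Its base size reads: "a sample size of 46 patients with SCI, 23 in each group, is sufficient to detect a between-group difference for the primary outcome measure". The calculation is for a two-sample t-test at 80% power and the 5% level. The section then makes an allowance for loss, which it justifies by the six-month follow-up: "a 30% conservative dropout rate was considered. Hence, 60 participants in total will be recruited for this study".

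The *Randomisation* section gives equal allocation: "participants will be randomly allocated (1:1) to an ACET group or a standard care control group". This takes place after the four-week assessment. The Abstract repeats the total of 60.

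The sample-size section does not state whether the 5% level is one- or two-sided, how the total was inflated for dropout, or which assessment the powered comparison uses.

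**The concern.** The section presents 60 as following from two inputs, 46 evaluable participants and 30% dropout. It does not follow from them: taking 30% from 60 gives a number below 46.

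This is the only sample-size justification in the article. A reader will take it that the trial still has 80% power if the full allowance is used up. The allowance is also called conservative, yet it covers less loss than it names. At stake are a few points of power and the accuracy of a statement that will probably be repeated in the trial report.

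**Working it through.** **Inputs** (from *Study population and sample size*, except allocation, which is from *Randomisation*): d = 0.85; independent t-test; 5% level; 80% power; 46 evaluable, 23 per group; 1:1 allocation; 30% dropout; 60 recruited.

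**Step 1: reproduce the base size.** Power comes from the noncentral t distribution with 2n − 2 degrees of freedom and noncentrality d × √(n/2), where n is the number per group. With a two-sided 5% level and d = 0.85:

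- n = 22: 78.6%
- n = 23: 80.5%

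So 23 per group is the smallest size that reaches 80%, and 46 is reproduced exactly. A one-sided 5% level needs only 18 per group and does not reproduce 46, so two-sided is taken as the intended level. Because 23 is the minimum, the base has no slack to absorb a shortfall.

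**Step 2: inflate for dropout.**

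- Dividing by the retained fraction: 46 / (1 − 0.30) = 65.7, so 66.
- Multiplying by one plus the dropout rate: 46 × 1.30 = 59.8, so 60.

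The stated 60 matches the second calculation and not the first. That the second was used is an inference.

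**Step 3: check 60 directly.** This needs no assumption about the formula.

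- 60 × 0.70 = 42, or 21 per group, four short of 46.
- Power at 21 per group and d = 0.85: 76.7%.
- Effect detectable with 80% power at 21 per group: d = 0.886, about 0.89.
- Largest loss that leaves 46: 1 − 46/60 = 23.3%, or 14 of 60.

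If loss is random, at 30% in each group of 30, so that group sizes vary, power averaged over the possible outcomes is 76.1%. The conclusion is the same.

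**Step 4: power over a range of loss.** The time point is not named, so the loss at the powered comparison is not known. Only the 30% row uses a loss rate from the protocol; 23.3% is derived above and the others are assumptions that show the range.

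| Total loss from 60 | Evaluable | Per group | Power at d = 0.85 |
|---|---|---|---|
| 0% | 60 | 30 | 89.9% |
| 10% | 54 | 27 | 86.5% |
| 20% | 48 | 24 | 82.2% |
| 23.3% | 46 | 23 | 80.5% |
| 30% | 42 | 21 | 76.7% |

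**The case against.** The strongest reply concerns timing. The 30% is tied to the six-month follow-up, which is T3, whereas the first objective is sitting balance after eight weeks of training, which points to T2. If the powered comparison is at T2, loss by then may be well under 30%, and 60 recruits would be enough for any loss up to 23.3%. This stands as a limit on the consequence: the loss of power is conditional. It does not repair the statement, because the section applies the 30% to its only powered comparison and derives 60 from it.

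A second reply is that the shortfall is small: four participants and 3.3 points below 80%. The effect size itself comes from a feasibility study, and its uncertainty probably matters more. That is fair, and it settles the severity.

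Three stronger readings are tempting, and the document does not support them:

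- **That a wrong formula was shown to have been used.** No formula is printed. The match with 46 × 1.3 makes it likely, but the inconsistency rests on 60 × 0.70 = 42 alone.
- **That the trial is underpowered and must recruit 66.** This would need the 30% loss to apply at the powered comparison, which is not established.
- **That losses between consent and the four-week randomisation reduce the 42 further, so that 60 must mean participants randomised.** The article refers to 60 recruited, gives no expected loss before allocation, and does not confine the 30% to losses after it. Those losses may already be included. Redefining the 60 as randomised would depart from the stated plan and could raise recruitment.

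**Conclusion.** The sample-size statement is internally inconsistent. The need for 46 evaluable participants is correct for d = 0.85, but 60 recruits with 30% loss provide 42. Nothing else in the article resolves this.

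The inconsistency itself is certain and can be checked by hand. Its effect on power is modest and conditional: 76.7% instead of at least 80% if the 30% loss applies to the powered comparison, and no shortfall if total loss by that comparison is 23.3% or less. The power figures assume a two-sided 5% level (the only one that reproduces 46), equal loss in the two groups, and the t-test named in the section. This is a correction worth making before results are known, and it is not a threat to the trial's validity.

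**What to change.** Replace the dropout sentence with wording such as: *With 60 recruited, 80% power at d = 0.85 is kept for up to 23% total loss between recruitment and the primary analysis; at 30% loss (42 evaluable) power is 77%.* Add the time point, T2 or T3, to which both the power and the loss figure apply.

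Counting loss from recruitment covers any withdrawal before allocation, so the 60 can stay defined as recruited. The cost is one corrected sentence and a slightly less favourable statement of the dropout that the trial can absorb. No extra participants are needed. Keeping 80% power at a full 30% loss would instead take 66 recruits, six more; that is the sponsor's choice and is not needed to make the text correct.

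### The 60 are counted at recruitment, about four weeks before randomisation, so losses before allocation use up places that the power calculation needs if the 30% allowance is also spent afterwards (minor).

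*Protocol article*

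**What the plan says.** All references are to the protocol article.

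- **Required number** (Study population and sample size): "a sample size of 46 patients with SCI, 23 in each group, is sufficient to detect a between-group difference", "using an independent t-test with 80% power and a 5% level of significance", at an effect size of d = 0.85 from the feasibility study.
- **Allowance for loss** (same section): "To account for a 6-month follow-up after discharge, a 30% conservative dropout rate was considered".
- **Target** (same section): "Hence, 60 participants in total will be recruited for this study".
- **Consent** (Recruitment and consent process): "The research team will obtain written informed consent from all participants prior to any data collection". Recruitment therefore precedes T0.
- **Period before allocation** (Randomisation): "All participants will undergo one baseline assessment and one 4-week assessment to estimate individuals’ spontaneous recovery rate".
- **Allocation** (Randomisation): "After the 4-week assessment, participants will be randomly allocated (1:1) to an ACET group or a standard care control group".

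The article gives no number to be randomised. Two other places bear on the point. The Assessments section expects every participant to have the baseline and 4-week assessments at the spinal units. Table 1 lists T1 under its postallocation heading, which does not agree with the Randomisation section.

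**The concern.** The target and the power calculation refer to different points in the trial. The 23 per group enter a between-group t-test, so they must be people who were allocated and then assessed. The 60 are people recruited, about four weeks earlier. Anyone who leaves between T0 and allocation takes one of the 60 places but belongs to neither arm.

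The only step from 46 to 60 is the 30% allowance, and its only stated reason lies at the far end of the trial. On the plan's own arithmetic that allowance takes all 60 places. If recruitment stops at 60 and the allowance is then used in full after allocation, each loss before allocation lowers the number analysed and so the power.

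What is at stake is precision, not validity: people who leave before allocation cannot bias the comparison between arms.

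**Working it through.** **Inputs.** From the sample size section: d = 0.85, 5% significance, 46 evaluable (23 per group), 30% dropout, 60 recruited. The section does not say whether the test is one- or two-sided; two-sided is taken because it reproduces the 46. The rate of loss between T0 and allocation, r, is not in the article. It is an assumption, shown as a range.

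**1. The plan's figures.** Power of the two-sided two-sample t-test comes from the noncentral t distribution with n₁ + n₂ − 2 degrees of freedom and noncentrality d × √(n₁n₂/(n₁ + n₂)).

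- 23 per group: 80.5%; 22 per group: 78.7%. So 46 is reproduced.
- 46 × 1.3 = 59.8, rounded to 60. So 60 is reproduced, by multiplying by 1 + 0.30.
- Dividing by the retained fraction would give 46 / 0.7 = 65.7, or 66.

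**2. No loss before allocation, full 30% after it.** 60 × 0.7 = 42 evaluable, 21 per group, power 76.7%. This shortfall exists without any early loss. It comes from multiplying instead of dividing, which is a separate error, and 76.7% is the right baseline for the present point.

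**3. Loss before allocation, then the full 30% (the T3 case).** Evaluable = 60 × (1 − r) × 0.7.

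| r (assumed) | Randomised | Evaluable | Power |
|---|---|---|---|
| 0% | 60 | 42.0 | 76.7% |
| 5% | 57 | 39.9 | 74.4% |
| 10% | 54 | 37.8 | 72.0% |
| 15% | 51 | 35.7 | 69.4% |

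Rounding to whole participants (40, 38, 36) gives 74.5%, 72.2% and 69.8%. Early loss itself therefore costs about 2 to 3 percentage points of power for each 5% lost.

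**4. Loss before allocation only (the best case at T2).** Analysed = 60 × (1 − r).

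| r (assumed) | Analysed | Power |
|---|---|---|
| 0% | 60 | 89.9% |
| 10% | 54 | 86.5% |
| 15% | 51 | 84.5% |
| 20% | 48 | 82.2% |
| 25% | 45 | 79.6% |

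The margin is 60 − 46 = 14 people, and 14/60 = 23.3% of those recruited.

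**5. Recruits needed to randomise 60.** 60 / (1 − r), rounded up, is 64, 67 and 71 at r = 5%, 10% and 15%: 4, 7 and 11 extra consents.

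**The case against.** The strongest reply is that the plan contains no demonstrated shortfall from early loss. A reader might infer that the 30% excludes losses before allocation and that every such loss comes straight off the stated 80%. The text supports neither inference.

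- **What the 30% covers.** The section gives post-discharge follow-up as the reason for a rate it calls conservative. It does not say that earlier losses are excluded, and a single overall attrition figure is a possible reading. This stands. But the text does not say that earlier losses are included either, so a clarification is needed on both readings.
- **Power at T2.** The first objective concerns sitting balance after 8 weeks of ACET. At that point 14 of 60 can be lost, from all causes together, before fewer than 46 remain. This stands. The lower figures apply only where the full 30% is also spent, as the plan foresees for the 6-month follow-up. T3 cannot be set aside, since no single primary time point is named.
- **Likely size of the loss.** Both early assessments are expected at the spinal units, so loss through discharge before T1 may be small. This stands. The 5–15% range is an assumption and not an estimate.
- **Source of the 77%.** The fall from 80% to 76.7% belongs to the inflation error and should not be charged to this point. This stands.
- **Loose wording.** Recruited may be meant as entered into the randomised comparison; the abstract speaks of evaluating ACET in 60 individuals. That is possible, and if so the fix is one word.
- **Material not shown.** A replacement rule may be in the full protocol or the flow chart. Its absence here is therefore not counted. The point rests on where the article itself places its stated number.

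**Conclusion.** The point holds in a limited form. The target of 60 is fixed at recruitment, about four weeks before randomisation, while 23 per group describes people allocated and assessed. The one allowance is justified by later follow-up, and 46 × 1.3 leaves nothing over if it is fully used after allocation.

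The effect is conditional. With 30% lost after allocation, assumed early losses of 5–15% lower power from 76.7% to between about 74% and 69%. With early loss alone, power stays above 80% unless more than 14 of the 60 go. These figures assume d = 0.85, a two-sided 5% test and nearly equal arms. No bias arises. Severity is minor: a number to be pinned to the right point in the trial, plus one inconsistency between Table 1 and the text.

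**What to change.** In Study population and sample size, do one of the following:

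1. **Count at randomisation (preferred).** State that 60 participants, 30 per group, will be randomised, and that people who leave before allocation do not use up places. At 5–15% early loss this costs about 4 to 11 extra consents with their baseline visits, and no extra ACET courses.
2. **Keep the cap at 60 recruited.** State which losses the 30% is meant to cover, and restate the expected evaluable number and its power: at most 42 and about 77% if 30% are lost after allocation, and lower with any loss before it. The only cost is a less favourable stated power.

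The first option does not repair the inflation error, which still leaves 42 evaluable after 30% loss; that needs its own correction. Under either option, use the same term for the 60 in the abstract, and reconcile Table 1 with the Randomisation section on whether T1 comes before or after allocation. These are wording changes only.
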